#### Sample size calculation

The sample size was calculated using Open Epi (available on www.openepi.com), for a two arm randomized controlled trial. With 80% power, a significance level of 5%, two sided-tests, assuming that adherence levels to ART overall are 90% in Africa. The adherence level of moderate alcohol users compared to abstainers and minimal alcoholusers shows an odds ratio of 0.480^27^. The minimum sample size for each group is 251 patients. To accommodate a drop-out rate of 10% overall, the sample size for each group will be 276, making a total of 552 patients.

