# Data Analysis

*Definition of virological failure:*

We follow the definition used in the national guidelines in which virological failure is defined as a repeat VL ≥ 1000 copies/ml after intense adherence assessment^38^.

*Definition of immunological failure:*

Immunological failure is defined according to the WHO definition. Failure is defined as a fall of CD4 count to pretherapy baseline (or below), *or* a 50% fall from the on-treatment peak value (if known) *or* a persistent CD4 levels below 100 cells/mm^3^.^39^

Means, standard deviations, and percentages will be used for descriptive statistics. T-test for continuous data and chi-square for categorical data will be used to examine differences between groups. Generalized Linear Model Repeated Measures 2 x 3 Analysis of Variance (ANOVA) will be used for comparing observations (alcohol use score) across the three contact periods to demonstrate a treatment intervention x time interaction.Observations with a single follow-up point missing (at either 3 and 12 months) will be imputed with the available follow-up. Data for participants who are lost to follow-up at 3 and 12 months will be imputed using baseline values. SPSS for Windows version 18.0 (SPSS, Inc., Chicago, IL) will be used for calculations.

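### The 10% drop-out allowance is multiplied rather than divided (276 instead of 279 per group), and it does not match the rule that keeps patients lost at both visits at baseline values

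*Protocol*

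**What the plan says.** Protocol, Sample size calculation. The design values are given as "With 80% power, a significance level of 5%, two sided-tests, assuming that adherence levels to ART overall are 90% in Africa". The effect comes from a cited meta-analysis: "The adherence level of moderate alcohol users compared to abstainers and minimal alcoholusers shows an odds ratio of 0.480". The result is "The minimum sample size for each group is 251 patients", followed by the allowance: "To accommodate a drop-out rate of 10% overall, the sample size for each group will be 276, making a total of 552 patients".

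Protocol, Data Analysis. Two imputation rules come directly after the repeated-measures ANOVA of the alcohol score. For one missed visit: "Observations with a single follow-up point missing (at either 3 and 12 months) will be imputed with the available follow-up". For both: "Data for participants who are lost to follow-up at 3 and 12 months will be imputed using baseline values".

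The sample size section does not say how drop-outs enter the analysis. It also does not split the 10% into patients who miss one follow-up and patients who miss both.

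**The concern.** There are two separate points.

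The first is arithmetic. To have 251 patients left after losing 10%, 251 must be divided by 0.90. Multiplying by 1.10 gives a number that falls back below 251 once the loss is taken off.

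The second is consistency. Adding patients for drop-out makes sense when drop-outs leave the analysis and the number analysed falls. Under the baseline-value rule nobody leaves: a patient lost at both visits is counted with a value that cannot carry any effect of the intervention. The number analysed stays the same and the expected difference between arms shrinks, and the sample size makes no allowance for that.

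At stake is whether 552 patients give the stated 80% power after a 10% loss, as a reader of the sample size section would take them to do.

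**Working it through.** **Inputs.** From the Protocol, Sample size calculation: two-sided 5%, 80% power, 90% reference adherence, odds ratio 0.480, equal groups, 10% drop-out. Baseline adherence b in the trial population is not given; I assume 75% to 90%. The share d lost at both visits is not given; I vary it up to the full 10%.

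**Reproducing 251.** The odds at 90% are 9. Then 9 × 0.48 = 4.32, and 4.32/5.32 = 0.812, a difference of 0.088. The mean rate is 0.856. With the pooled-variance formula

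n = (1.960 + 0.842)² × 2 × 0.856 × 0.144 / 0.088² = 250.02 with unrounded inputs,

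which rounds up to 251, the stated minimum. The Fleiss formula gives 249 and the unpooled formula 247.

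**The allowance.**
- 251 × 1.10 = 276.1, the stated 276.
- 276 × 0.90 = 248.4, so 248 remain, 3 below the minimum.
- 251 / 0.90 = 278.9, so 279 per group, 558 in total.

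**Power if drop-outs leave (248 per group, 90.0% v 81.2%).** The Fleiss form is

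power = Φ[(Δ√n − 1.96 √(2p̄(1−p̄))) / √(p₁(1−p₁) + p₂(1−p₂))]

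= Φ[(0.0880 × 15.75 − 1.96 × 0.4965) / 0.4926] = Φ(0.837) = 79.9%.

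The pooled formula gives 79.7% and the unpooled formula 80.3%.

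**Power if a share d is carried at baseline (276 per group).** The arms become (1 − d) × 0.900 + d × b and (1 − d) × 0.812 + d × b, so the difference is (1 − d) × 0.088. Patients who miss only one visit take the other follow-up value and are not reset to baseline; I treat them as keeping the full effect.

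For d = 10% and b = 81.2%, the arms are 89.1% and 81.2% and the difference is 7.9 points. Power = Φ[(0.0792 × 16.61 − 1.96 × 0.5027) / 0.4996] = Φ(0.66) = 74.6%. The same formula over the assumed range gives:

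| Share lost at both visits | b = 75% | b = 81.2% | b = 90% |
| --- | --- | --- | --- |
| 10% | 73.1% | 74.6% | 76.7% |
| 7% | 76.6% | 77.6% | 79.0% |
| 5% | 78.8% | 79.5% | 80.5% |

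At 3% it is about 81–82%.

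**Does 279 cure the second point?** No. With d = 10%, 279 per group gives 73.6% to 77.1%. Reaching 80% under that rule would take 327 (b = 75%), 316 (b = 81.2%) or 300 (b = 90%) per group.

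**The case against.** The strongest reply is that neither part does much harm. With drop-outs left out, the gap is 3 patients per group and at most 0.3 points of power, and it vanishes under the unpooled formula. That stands: the inflation slip is of rounding size in its effect, although the figure itself is wrong.

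On the second part, a reader might infer that the plan's written rule clearly drops power to about 75%, so that 80% is missed however drop-outs are handled. The Protocol does not support that reading, for three reasons.

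- Baseline values are prescribed only for patients lost at both visits; a single missed visit takes the other follow-up value. The 10% is given overall and not split. The Procedure section plans at least six contact attempts and further attempts at the next follow-up point, so losses at a single visit are expected.
- The imputation sentences directly follow the alcohol-score ANOVA, whereas the sample size rests on adherence. Their wording is general and no other missing-data rule is given, so covering adherence is a fair reading but not an established one. The VAS is taken at baseline only for patients already on ART, so others would have no VAS value to carry forward.
- Baseline adherence is not stated, so any power figure under the rule rests on an assumed value.

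These limits stand, and they make the second part conditional. They do not remove the mismatch: an allowance that adds patients does not address dilution, and the sample size section does not say which handling it assumes.

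**Conclusion.** The allowance is miscalculated: 276 per group does not leave 251 after a 10% loss, and 279 does. If drop-outs leave the analysis, the consequence is negligible, with power of 79.7–80.3%.

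The allowance and the baseline-value rule also describe different handling of the same patients. How much this matters depends on the share lost at both visits, and it assumes that the rule covers adherence and that baseline adherence lies between 75% and 90%. The shortfall is about 3 to 7 points if the full 10% are lost at both visits, about 1 to 3 points at 7%, and not material at 5% or below. The lowest power, about 73–77%, is the extreme of the range and not the expected result.

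The point is minor.

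**What to change.** In the Protocol's Sample size calculation, do one of two things:
- correct the inflation to 251/0.90 = 279 per group, 558 in total; or
- keep 552 and state that a 10% loss leaves 248 per group, with power of about 80% for observed data.

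In either case, add the assumed share of patients lost at both visits and the power under the baseline-value rule for that share (at 276 per group, down to about 73–77% if it is the full 10%). Say whether the imputation rules in Data Analysis apply to adherence, so that the adherence power statement and the adherence analysis handle drop-outs in the same way. Moving to 279 alone does not resolve the mismatch.

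The cost is a few sentences and a slightly less favourable stated power. Keeping 552 adds no patients; correcting to 558 adds 6.

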#### Procedure

The procedure follows the procedure of the main protocol.

Universal screening of all presenting HIV out-patients will be done. All consecutive HIV positive clients visiting the out-patient department will be screened for alcohol problems and randomized into an intervention or control group. Randomization will be done by a remote computer to generate numbers for intervention and control. Research assistant 1 will ask for consent from patients attending the hospital out-patient department to participate in the study, i.e. do a baseline assessment using the AUDIT questionnaire. Research assistant 1 will not be involved in delivering treatment. Research assistant 2 will score the results of the alcohol test section of the questionnaire. Clinic out-patients who score 8-19 for men and 7-19 for women on the AUDIT questionnaire after screening (risky drinkers) will be included in this study. Patients with a score of 20 and above on the AUDIT (with probable alcohol dependence) will be referred for further management. Additional information of the patients will be collected using the data collection instruments. Research assistant 2 will then check the random numbers which allocate the case to the intervention arm or control arms. Research assistant 2 will carry out the intervention for all the participants, after which they will be followed up at 3 and 12 months (which are standard visit intervals for the follow up of the HIV care), and assessments will be done by Research assistant 1, who will be blinded to the intervention allocation of the participants. In the event of a drop-out, at least six individual attempts will be made to contact patients by telephone and letter. Even if a contact was not successful at either follow up point, further attempts will be made at any next follow up point. Sampling will occur throughout all hours of clinic operation over a 3-month period. Two-hundred and seventy six patients will be recruited from hospital out-patient departments. Patients will be offered a drink (soda, water) during the interviews.

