# Time line and research activity

| **Research Activity** | **Month/Year** |
| --- | --- |
| Phase 1: Ethics approval and field preparation  1) Full ethics protocol submission  2) Preparatory visits to health facilities  3) Recruitment and training of research assistants/counselors  4) Pre-test and printing of questionnaires  Phase 2: Recruitment of 552 participants  1) Brief interventions of alcohol problems  2) Project management meetings, teleconferences  3) Interview Quality control  4) Data entry/ analysis and publication    Phase 3: First follow-up interviews with participants (3 months)  1) Interviews  2) Project management meetings  3) Quality control  4) Data entry/ analysis/Publication  Phase 4: Second follow-up interviews with participants (12 months)  1) Interviews  2) Project management meetings  3) Quality control  4) Data entry/ analysis/Publication | July-Aug 2011  Aug 2011  Aug 2011  Aug 2011  Sept-Nov 2011  Sept-Nov 011  Sept-Nov2011  Dec 2011  Dec-Feb 2012  Dec-Feb 2012  Dec- Feb 2012  Feb-Apr 2012  Oct-Dec 2012  Oct- Dec 2012  Oct- Dec 2012  Jan-Feb 2013 |

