# Budget

| **Activities** | **Budget (R)** |
| --- | --- |
| Teleconference with research team and consultant in Belgium | R 4,000 |
| Salaries 2 full time field workers # R 6000 pm x 6 months | R 72,000 |
| Top up pharmacy assistant adherence measurement | R 5,000 |
| Training the field workers | R 2,000 |
| Pre-testing questionnaires | R 1,000 |
| Printing questionnaires, inform consent, reports | R 6,000 |
| Data/ interview quality control | R 3,000 |
| Recruitment and first interview (drink) R 6 per case x 552 | R 3,312 |
| 1^st^ and 2^nd^ follow up ( R 12 x 552) | R 6,624 |
| Telephone for follow up | R 4,000 |
| Data entry ( R 10 X 552 X 4) | R 22,080 |
| Publication fee and editing (expected 5 papers) | R 30,000 |
| **Total** | **R 159,016** |

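### The Procedure gives the per-group number, 276, as the number of patients to be recruited, while the sample size section, timetable and budget all use 552

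*Protocol*

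**What the plan says.** Four sections of the protocol bear on the number to be enrolled.

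- **Sample size calculation:** "The minimum sample size for each group is 251 patients". After an allowance for 10% drop-out, "the sample size for each group will be 276, making a total of 552 patients".
- **Procedure:** "Sampling will occur throughout all hours of clinic operation over a 3-month period", followed at once by "Two-hundred and seventy six patients will be recruited from hospital out-patient departments". Nothing in that sentence or around it marks 276 as a per-group figure.
- **Time line and research activity:** "Phase 2: Recruitment of 552 participants", dated September to November 2011, which is also three months.
- **Budget:** "Recruitment and first interview (drink) R 6 per case x 552". The follow-up line and the data entry line also multiply by 552.

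**The concern.** The Procedure is the section that describes the fieldwork: who screens, who scores, who looks up the allocation and who follows up. Its recruitment number is half the total on which the rest of the protocol is built. The number equals the per-group size in the section just before it, so the likely cause is a lost qualifier.

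Enrolment is the quantity on which the power statement rests. If the Procedure's number were taken as the total, each arm would fall well below the minimum that the protocol sets for itself. A shortfall found after the three-month recruitment window had closed would be hard to make good.

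**Working it through.** **Inputs, all from the Sample size calculation section unless noted**

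- Reference adherence 90%; odds ratio 0.480; two-sided 5%; power 80%.
- Minimum 251 per group; 10% drop-out; 276 per group; 552 in total.
- Recruitment number in the Procedure: 276.

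**Step 1: reproduce the protocol's figures**

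Odds at 90% are 0.9/0.1 = 9. Shifted by the odds ratio: 0.480 × 9 = 4.32, so p2 = 4.32/5.32 = 0.812. The difference is d = 0.900 − 0.812 = 0.088 (0.08797 unrounded), and the mean proportion is 0.856.

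The normal-approximation sample size per group, without continuity correction, is

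n = [1.960 × √(2 × 0.856 × 0.144) + 0.842 × √(0.9 × 0.1 + 0.812 × 0.188)]² / d² = 249.

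The protocol states 251, which is close enough to confirm that these are its inputs. Then 251 × 1.1 = 276.1, giving 276 per group, and 2 × 276 = 552.

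**Step 2: check which total the other sections use**

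| Place | Arithmetic | Patients |
| --- | --- | --- |
| Sample size calculation | 2 × 276 | 552 |
| Time line, recruitment phase | stated | 552 |
| Budget, recruitment and first interview | R 3,312 / R 6 | 552 |
| Budget, both follow-ups | R 6,624 / R 12 | 552 |
| Budget, data entry | R 22,080 / (R 10 × 4) | 552 |
| Procedure | stated | 276 |

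The Procedure is the only outlier, and 276/552 = 50%.

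**Step 3: what 276 in total would mean**

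Split equally, 276/2 = 138 per arm; after 10% drop-out, 138 × 0.9 = 124.2, about 124. With the same approximation,

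power = Φ{[d√n − 1.960 × √(2 × 0.856 × 0.144)] / √(0.9 × 0.1 + 0.812 × 0.188)}.

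| Patients per arm | How it arises | Power |
| --- | --- | --- |
| 251 | stated minimum | 80.3% |
| 276 | 552 recruited, no drop-out | 83.9% |
| 248 | 552 recruited, 10% drop-out | 79.9% |
| 138 | 276 recruited in total, no drop-out | 54.9% |
| 124 | 276 recruited in total, 10% drop-out | 50.5% |

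**The case against.** The strongest reply is that the intended number is not in doubt. The section immediately before the Procedure states both the per-group size and the total, and the timetable and every per-case budget line repeat the total. A team would have to overlook all three to stop at 276. That stands. It makes the loss of power a conditional consequence, not a property of the design. It does not make the sentence right.

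Two readings might seem to rescue the sentence. One is that 276 is only the part coming from hospital out-patient departments, with the rest coming from elsewhere. No section assigns a second 276 to another source. The hospital and clinic wording does not settle the matter either way: the Problem statement speaks of clinics under the hospital, and the Procedure uses both terms. The other is that the Procedure opens by deferring to a main protocol. That does not reconcile the figures, because this trial's size is fixed in its own sample size section.

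Two stronger readings are also tempting and are not supported. A reader might infer that the Procedure orders recruitment to stop at 276. It contains no stopping rule, only a number and a three-month window, and the timetable separately gives both a number and dates. A reader might also infer that the timetable's follow-up phases are set at 552. They carry no number; for follow-up, 552 comes from the budget.

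**Conclusion.** The Procedure's recruitment number is wrong as written: it is half the total that the sample size section, the timetable and the budget agree on. That conclusion needs no assumption.

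The size of the harm is conditional. If 276 were taken as the total with equal allocation, there would be 138 patients per arm (about 124 after drop-out) against the stated minimum of 251, and power of about 55% (about 51% after drop-out) against the stated 80%. These figures take the protocol's adherence assumptions as given and use the normal approximation. They do not show that the planned trial is underpowered: with 552 recruited and 10% drop-out, power on the same inputs is about 80%, as the protocol intends.

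**What to change.** In the Procedure, change the number in the recruitment sentence so that it reads: *552 patients (276 per group) will be recruited*. The Sample size calculation, timetable and Budget sections already use 552 and need no change.

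The cost is one corrected sentence. No patients, time or money are added, since the recruitment phase and the budget already provide for 552. The correction should be made before recruitment begins, while it is still free.

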# Data collection instruments

Three instruments will be use to collected data: i) questionnaire and screening test, ii) patients information extract sheet, and iii) Assesment of adherence to ART by VAS and pill count form in the pharmacy.

#### Questionnaire and screening test (Annex 1)

###### Demographic Characteristics

A researcher-designed questionnaire will be used to record information on participants’ age, gender, educational level, marital status, income, and residential status. This questionnaire will be used at baseline. At every follow up visit changes will be checked briefly.

######

###### Sexual behavior

To study the sexual behavior of HIV patients who consume moderate amounts of alcohol before and after intervention, we included a questionnaire with questions on sexual behavior. This questionnaire will be administered at baseline and every follow up visit.

#### Health and quality of life related questionnaires (annex 2)

###### Health-related quality of life (QoL)

The WHOQoL-HIVBREF is based on the WHOQOLHIV measure, one of the two World Health Organization’s (WHO) QoL instruments for the use with HIV infected populations^28,29^. This questionnaire will be taken at baseline, and every follow up visit.

###### Depression

We will assess depressive symptoms using the 10-item version of the Centers for Epidemiologic Studies Depression Scale (CES-D)^30^. The CES-D has been widely used in studies of the relationship between HIV and depression^31^. The sensitivity and specificity of the CES-D 20-item survey has been reported to average 80% and 70%, respectively, compared to formal diagnostic interview^32^. We will also identify patients who experience more severe depressive symptoms by distinguishing those scoring greater or equal to 15 out of 30 on the CES-D 10-item survey^30^. This questionnaire will be taken at baseline and every follow up visit.

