| 16 Have you got enough money to meet your needs? | | | [ ] 1. | [ ] 2. | | [ ] 3. | | | [ ] 4. | | | [ ] 5. |
| 17 To what extent do you feel accepted by the people you know, whether or not they are aware of your HIV/AIDS? | | | [ ] 1. | [ ] 2. | | [ ] 3. | | | [ ] 4. | | | [ ] 5. |
| 18 How available to you is the information that you need in your day-to-day life? | | | [ ] 1. | [ ] 2. | | [ ] 3. | | | [ ] 4. | | | [ ] 5. |
| 19 To what extent do you have the opportunity for leisure activities? | | | [ ] 1. | [ ] 2. | | [ ] 3. | | | [ ] 4. | | | [ ] 5. |
| 20 How well are you able to get around? | | | [ ] 1. | [ ] 2. | | [ ] 3. | | | [ ] 4. | | | [ ] 5. |
|  | | | **Very dissatisfied** | **Dissatisfied** | | **Neither satisfied nor dissatisfied** | | | **Satisfied** | | | **Very satisfied** |
| 21 How satisfied are you with your sleep? | | | [ ] 1. | [ ] 2. | | [ ] 3. | | | [ ] 4. | | | [ ] 5. |
| 22 How satisfied are you with your ability to perform your daily activities? | | | [ ] 1. | [ ] 2. | | [ ] 3. | | | [ ] 4. | | | [ ] 5. |
| 23 How satisfied are you with your capacity to work? | | | [ ] 1. | [ ] 2. | | [ ] 3. | | | [ ] 4. | | | [ ] 5. |
| 24 How satisfied are you with yourself? | | | [ ] 1. | [ ] 2. | | [ ] 3. | | | [ ] 4. | | | [ ] 5. |
| 25 How satisfied are you with your personal relationships? | | | [ ] 1. | [ ] 2. | | [ ] 3. | | | [ ] 4. | | | [ ] 5. |
| 26 How satisfied are you with your sex life? | | | [ ] 1. | [ ] 2. | | [ ] 3. | | | [ ] 4. | | | [ ] 5. |
| 27 How satisfied are you with the support you get from your friends? | | | [ ] 1. | [ ] 2. | | [ ] 3. | | | [ ] 4. | | | [ ] 5. |
| 28 How satisfied are you with the condition of your living space? | | | [ ] 1. | [ ] 2. | | [ ] 3. | | | [ ] 4. | | | [ ] 5. |
| 29 How satisfied are you with your access to health services? | | | [ ] 1. | [ ] 2. | | [ ] 3. | | | [ ] 4. | | | [ ] 5. |
| 30 How satisfied are you with your transport? | | | [ ] 1. | [ ] 2. | | [ ] 3. | | | [ ] 4. | | | [ ] 5. |
| **The following question refers to how often you have felt or experienced certain things in the last two weeks.** | | | | | | | | | | | | |
| 31 How often do you have negative feelings such as depressed mood, despair, anxiety? | [ ] 1. Never | [ ] 2. Seldom | | | [ ] 3. Quite often | | | [ ] 4.Very often | | | [ ] 5. Never | |

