###### Depression:

| **CES-D** | | | | |
| --- | --- | --- | --- | --- |
| **For each of these statements, please indicate how often you felt this way during the past week** | | | | |
|  | Rarely (<1day) | Some/little (1-2 days) | Much  (3-4 days) | Most  (5-7 days) |
| 1. I was bothered by things that usually don’t bother me | 1 | 2 | 3 | 4 |
| 2. I had trouble keeping my mind on what I was doing | 1 | 2 | 3 | 4 |
| 3. I felt that everything I did was an effort | 1 | 2 | 3 | 4 |
| 4. I felt depressed | 1 | 2 | 3 | 4 |
| 5. I felt hopeful about the future | 1 | 2 | 3 | 4 |
| 6. I felt fearful | 1 | 2 | 3 | 4 |
| 7. My sleep was restless | 1 | 2 | 3 | 4 |
| 8. I was happy | 1 | 2 | 3 | 4 |
| 9. I felt lonely | 1 | 2 | 3 | 4 |
| 10. I could not get going | 1 | 2 | 3 | 4 |

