**In the past 3 months –How many times did you……**

| 1. Have sex **without** condoms (protection)? | 0 | 1-2 | 3-5 | 6-10 | 11-20 | 21-30 | 31-40 | 41 or more times |
| --- | --- | --- | --- | --- | --- | --- | --- | --- |
| 1. Have sex **with** use of condoms (protection)? | 0 | 1-2 | 3-5 | 6-10 | 11-20 | 21-30 | 31-40 | 41 or more times |
| 1. Drank alcohol before sex? | 0 | 1-2 | 3-5 | 6-10 | 11-20 | 21-30 | 31-40 | 41 or more times |
| 1. Your sex partner drank alcohol before sex? | 0 | 1-2 | 3-5 | 6-10 | 11-20 | 21-30 | 31-40 | 41 or more times |
| 1. Use drugs (Dagga, mandrax, or others) before sex? | 0 | 1-2 | 3-5 | 6-10 | 11-20 | 21-30 | 31-40 | 41 or more times |
| 1. Your sex partner used drugs (Dagga, mandrax, or others) before sex? | 0 | 1-2 | 3-5 | 6-10 | 11-20 | 21-30 | 31-40 | 41 or more times |

| 1. Use a condom at last sex, with partner whom unknown or negative HIV status | [ ] 1. Yes [ ] 2. No |
| --- | --- |
| 1. **In the past 3 months –I have** Disclosed my HIV status to my last sex partner | [ ] 1. Yes [ ] 2. No |

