| 31. Ke ga kae o ikutlwa o na le letshogo e bile moya wa gago o le ko tlase? | [ ] 1. Le go ka | [ ] 2. Go le gonnye | | | [ ] 3. Go le gontsi | | | [ ]4.Go le gontsi thata | | | [ ] 5. Le go ka | |

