###### Sexual Behaviour-Setswana

| **Sexual behaviour** | | | | | | |
| --- | --- | --- | --- | --- | --- | --- |
| Nagana sentle ka ga dikgwedi tse 3 tse di fitileng mme o tlhophe karabo ya gago. | | | | | | |
| 1. O ne wa tsena mo thobalanong mo kgweding tse tharo tse di fitileng? | Ee [ ] | Nya [ ] | Ga o re nya, e ya ko potso ya bolesome | | | |
| 2. O robalane le borre ba le bakae mo kgweding tse tharo tse di fitileng? | 0 | 1 | 2 | 3 | 4 | 5 kgotsa ba go feta |
| 3. O robalane le bomme ba le bakae mo kgweding tse tharo tse di fitileng? | 0 | 1 | 2 | 3 | 4 | 5 kgotsa ba go feta |

Jaanong nagana sentle ka ga dikgwedi tse 3 tse di fitileng.

Mo kgweding tse 3 tse di fitileng-Ke makgetho a le makae……

| 4. O tsene mo thobalanong ka ntle le go dirisa kgotlhopo? | 0 | 1-2 | 3-5 | 6-10 | 11-20 | 21-30 | 31-40 | 41 kgotsa ba go feta |
| --- | --- | --- | --- | --- | --- | --- | --- | --- |
| 5. O tsene mo thobalanong o dirisa kgotlhopo? | 0 | 1-2 | 3-5 | 6-10 | 11-20 | 21-30 | 31-40 | 41 kgotsa ba go feta |
| 6. O tsene mo thobalanong o nwele bojalwa? | 0 | 1-2 | 3-5 | 6-10 | 11-20 | 21-30 | 31-40 | 41 kgotsa ba go feta |
| 7. Molekane wa gago a nwele bojalwa pele le robalana? | 0 | 1-2 | 3-5 | 6-10 | 11-20 | 21-30 | 31-40 | 41 kgotsa ba go feta |
| 8. O dirisitse diritibatsi pele ga thobalano? | 0 | 1-2 | 3-5 | 6-10 | 11-20 | 21-30 | 31-40 | 41 kgotsa ba go feta |
| 9. Molekane wa gago a dirisitse diritibatsi pele ga thobalano? | 0 | 1-2 | 3-5 | 6-10 | 11-20 | 21-30 | 31-40 | 41 kgotsa ba go feta |

| 10. O ne wa se dirise kgolhopo le molekane yo o sa itseng maemo a gagwe a HIV | [ ] 1. Ee [ ] 2. Nya |
| --- | --- |
| **11. Mo kgweding tse 3 tse di fitileng –Ke itsisitse** Molekane wa bofelo o ke neng ka tsena mo thobalanong le ena ka maemo a me a HIV | [ ] 1. Ee [ ] 2. Nya |

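### Three Annex 2 items do not fit their scoring or their translation: the CES-D cut-off of 15 out of 30 against printed codes 1–4, a duplicated *Never* in quality-of-life item 31, and a Setswana condom item that appears negated

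*Protocol*

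**What the plan says.** **CES-D.** Under *Depression*, in the section on health and quality-of-life questionnaires, the protocol adopts the "10-item version of the Centers for Epidemiologic Studies Depression Scale (CES-D") and defines a higher-symptom group by "distinguishing those scoring greater or equal to 15 out of 30 on the CES-D 10-item survey". The English form in Annex 2 prints the codes 1, 2, 3, 4 against every item. That includes the two positively worded items: "I felt hopeful about the future | 1 | 2 | 3 | 4" (item 5) and "8. I was happy | 1 | 2 | 3 | 4". The Setswana form prints the same codes. Neither form, nor the section text, gives a recode or a reversal.

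**Quality-of-life item 31.** This asks how often the respondent has negative feelings. Option 1 is *Never*, and the English list ends "4.Very often | | | [ ] 5. Never". In the Setswana version option 1 is *Le go ka*, and the list ends "4.Go le gontsi thata | | | [ ] 5. Le go ka".

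**Condom item.** The English form reads "Use a condom at last sex, with partner whom unknown or negative HIV status". Item 10 of the Setswana form reads "O ne wa se dirise kgolhopo le molekane yo o sa itseng maemo a gagwe a HIV". Both store Yes as 1 and No as 2.

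The section on alcohol consumption says that all questionnaires are given in English or Tswana. Depression, quality of life and sexual behaviour are collected at baseline and at every follow-up.

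**The concern.** Each of these is a mismatch within the document itself, not detail that a protocol would normally leave to an analysis plan. The CES-D threshold belongs to a 0–30 scale that the printed codes do not produce. If the printed numerals are taken as scores, the classification is wrong, and on the two positive items it runs in the wrong direction. That reading is a natural one, because the AUDIT form in the same protocol prints its real scoring values (0–4).

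Item 31 offers no box for the highest frequency, and a respondent with no negative feelings can be entered at either end of the scale. Quality of life is a named between-arm comparison in Objectives 4(c) and 5(c) and in the hypotheses.

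If the Setswana condom item asks about non-use, code 1 means opposite things in the two languages. Sexual behaviour is part of Objectives 2 and 3.

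The protocol also states that all its instruments are standard, with proven validity and reliability. Forms with altered response options or a changed question do not carry that assurance with them.

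**Working it through.** **1. CES-D range**

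Inputs: 10 items and a maximum of 30 (*Depression*); codes 1–4 on every item (Annex 2, both languages).

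- Range implied by the cut-off: 30 / 10 = 3 per item, so items run 0–3 and the total 0–30.
- Range from the printed codes: 10×1 = 10 to 10×4 = 40. The stated maximum of 30 is not reproduced.
- With items 5 and 8 reversed, the two totals differ by a constant 10. A cut-off of 15 on the 1–4 total is 15 − 10 = 5 on the 0–30 scale. The equivalent of 15 out of 30 on the 1–4 total would be 15 + 10 = 25.

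**2. CES-D direction**

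Totals without reversal, as printed, against 0–3 scoring with items 5 and 8 reversed:

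| Response pattern (eight negative items all *Rarely*) | Printed sum | 0–3, reversed |
| --- | --- | --- |
| Items 5 and 8 both *Most* (no symptoms) | 8×1 + 2×4 = 16, flagged | 8×0 + 2×0 = 0 |
| Item 5 *Some*, item 8 *Much* | 8 + 2 + 3 = 13, not flagged | 0 + 2 + 1 = 3 |
| Items 5 and 8 both *Rarely* | 8×1 + 2×1 = 10, not flagged | 0 + 3 + 3 = 6 |

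The printed sum ranks these three patients in the reverse of their symptom order and flags only the one without symptoms. With items 5 and 8 reversed on the 1–4 codes, that patient scores 10 and is not flagged, but the effective threshold is then 5 out of 30.

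**3. Item 31**

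In each language the labels of codes 1 and 5 are identical, and code 4 is *Very often* or its Setswana counterpart. Two things follow. There is no label above *Very often*. And a recorded 5 may mean *Never*, or may mean that the box was used as the top of a rising scale. The two meanings are 5 − 1 = 4 points apart on a 5-point item, and nothing else on the form separates them.

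**4. Condom item**

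- English: affirmative (use), at last sex, with a partner of unknown or negative status.
- Setswana item 10: *wa se dirise*. Item 5 of the same form, on sex with a condom, has *o dirisa*. The contrast points to a negated verb in item 10.
- Setswana item 10 has no wording for last sex or for a partner of negative status.
- Codes: 1 = Yes and 2 = No in both.

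If the verb is negated, code 1 is condom use in English and non-use in Setswana. The two versions also differ in scope, so flipping the code would not make them equivalent.

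**The case against.** The best defence concerns the CES-D. The printed 1–4 can be read as response codes and not as scores. The form carries no instruction to total them, whereas the AUDIT form does, and the only scoring statement is the threshold out of 30, given with a citation for the short form. The quality-of-life form also prints uniform codes for items worded in opposite directions, and a scoring manual for that scale is cited. Reversal is the kind of detail a scoring guide often holds. This stands in part: no response is lost, and recoding from raw items gives the correct score. A constant offset of 10 also leaves between-arm differences in a continuous CES-D score unchanged. It does not remove the conflict between the stated cut-off and the printed codes, which the document leaves unresolved.

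A reader might infer that almost everyone would be classed as having severe depression. The documents do not support that. Unreversed totals start at 10, some patterns with few symptoms fall below 15, as shown above, and no score distribution is given for either way of scoring. The protocol's category is also one of more severe symptoms, not a diagnosis.

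On the condom item, a reader might conclude that the answer is inverted in every Setswana interview. That rests on reading one verb form; the document contains no back-translation.

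On item 31, an interviewer may well treat the fifth box as the top of the scale, since it follows *Very often*. The 4-point error is therefore a worst case, on one of 31 items. This limits the likely size but does not make a stored 5 interpretable.

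Finally, questionnaire pre-testing is planned and budgeted and might catch these slips. It is an opportunity to correct them, not a correction.

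**Conclusion.** The point holds for all three items, with different certainty.

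- **CES-D: certain, and recoverable.** The cut-off of 15 out of 30 does not fit the printed 10–40 total. Applied without recoding it flags a symptom-free patient at 16; with reversal alone it acts as 5 out of 30. The consequence depends on an analyst taking the printed codes as scores.
- **Item 31: certain, and not recoverable once data are collected.** The duplication appears in both language forms, so an error in reading the PDF is unlikely. How many respondents it would affect is unknown.
- **Condom item: probable.** The negation needs a back-translation to confirm it. The missing wording on last sex and negative status is a second reason not to pool the versions as they stand.

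The reach is limited. Depression is not named in the objectives, and sexual behaviour is not among the between-arm comparisons of Objectives 4 and 5. Quality of life is, through one item of 31. The alcohol score used in the repeated-measures analysis, the adherence measure and the sample size are untouched.

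**What to change.** 1. **CES-D.** State that items are scored 0–3 and that items 5 and 8 are reversed (3 minus the item score) before the threshold of 15 out of 30 is applied. If the printed 1–4 codes stay, reverse items 5 and 8 as 5 minus the code and subtract 10 from the total. Keep the raw item responses in the data set.
2. **Quality-of-life item 31.** Replace the label of option 5 with the frequency category above *Very often*, in English and in Setswana, before the forms are printed.
3. **Condom item.** Obtain an independent back-translation of Setswana item 10. Reword it to match the English: affirmative, at last sex, partner of unknown or negative status. Do not pool the two language versions until this is done.

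The cost is one or two lines of scoring text, two label changes and the back-translation of one item. The timeline already places pre-testing and printing of questionnaires in August 2011, before recruitment starts in September, and the budget has lines for both (R 1,000 and R 6,000). After data collection only the CES-D part could still be fully repaired.
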